## Abstract

**Background:**

Antimicrobial resistance (AMR) is associated with significant human and financial costs, particularly among vulnerable populations like older adults living in long-term care homes (LTCHs). Urinary tract infection (UTI) is the leading indication for antibiotic use in this population, with some estimates suggesting that up to 70% of these prescriptions may be avoidable.

**Objective:**

The purpose of this study is to develop and test novel behavioural science-informed antimicrobial stewardship (AMS) quality improvement strategies in Canadian LTCHs, which aim to decrease unnecessary testing and treatment for residents who lack the minimum clinical signs and symptoms of UTI.

**Intervention:**

The quality improvement strategy is a two-pronged approach that includes 1) targeted education for essential care providers (family and friends of LTCH residents) about UTI and benefits of AMS, which strives to outline a positive role for this group in UTI management, and 2) monthly feedback to LTCH staff on their facility’s urine culture ordering rates.

**Outcomes:**

The protocol was piloted in a single LTCH; a process evaluation of the pilot implementation served to refine the research protocol, which is being implemented in eight LTCHs across Canada using an eight-month stepped wedge randomized cluster design.

**Conclusion:**

This protocol represents a behavioural science-informed intervention to improve AMS across LTCHs. If successful, this model of care could be scalable across Canadian LTCHs, offering an inclusive approach that aims to empower clinicians, non-regulated healthcare staff, residents and their family and friends to improve health outcomes as antibiotic stewards.

## Introduction

The World Health Organization has identified antimicrobial resistance (AMR) as one of the top ten threats to global public health ((1)), with serious human and financial costs ((2)). Some Canadian estimates indicate that up to 50% of antibiotic prescriptions in outpatient settings ((3)), and nearly 25% in hospital settings ((4)), are avoidable. Residents of long-term care homes (LTCHs) are increasingly frail and particularly vulnerable to high rates of antibiotic use and antimicrobial-resistant infections ((5,6)), risk of adverse outcomes linked to avoidable antibiotic use ((7)) and relatively less developed antimicrobial stewardship (AMS) programs compared to other sectors ((8)). The leading indication for antibiotic use in LTCHs is urinary tract infections (UTI) ((9)), as it makes up over half of antibiotics prescribed in this sector ((10)), with up to 70.5% of these prescriptions considered clinically unnecessary ((9)). At the core of this challenge is the occurrence of asymptomatic bacteriuria, which is remarkably prevalent, being present in up to 50% of LTCH residents ((5,11)). Asymptomatic bacteriuria is the expected presence of bacteria in an appropriately collected urine specimen, in absence of clinical symptoms of UTI. Positive urine cultures that identify asymptomatic bacteriuria are frequently attributed to UTI for many non-specific presentations, which underscores the importance of limiting urine culture collection to situations where minimum clinical symptoms are present. An upstream focus on the judicious use of urine cultures is known to result in significant reductions in antibiotic use of asymptomatic bacteriuria ((12,13)) and may significantly improve AMS in LTCHs.

Evidence suggests that AMS interventions in LTCH can reduce antibiotic prescribing, especially for the treatment of UTI ((14–16)), including a recent meta-analysis showing a 14% overall reduction in antimicrobial use ((8)). Upstream interventions targeting urine culture, known as diagnostic stewardship interventions, may be most effective at reducing unnecessary antibiotic prescriptions for UTI ((10,12,13,17–20)). Importantly, a recent systematic review found AMS interventions did not increase risk of hospital admission or death, indicating that these programs did not lead to under-treatment of infection ((21)).

Behavioural science offers a useful lens for addressing antimicrobial resistance ((22)). Behavioural science frameworks have been used to understand the drivers and barriers affecting stewardship behaviours ((23)), as foundation for AMS interventions ((24–28)). In the current work, findings from an initial literature review ((29) were synthesized with stakeholder interview results into a series of mapping exercises that narrowed from a systems, to behaviour, to cognitive map. In this way, we formalized our understanding of how prescribing decisions are influenced by the context of the individual resident, their caregivers, the clinical environment, the healthcare system and the surrounding culture. We then used a barrier prioritization exercise with a working group of experts to identify barriers for our quality improvement (QI) strategies to address. This resulted in development of a two-pronged QI strategy for reducing diagnostic testing and antibiotic treatment of UTI when not clinically indicated. The first strategy consists of targeted education for essential care providers (ECPs; someone who provides important care for a resident and who is not on the medical team, e.g., family member or friend) to address ECP expectations for testing and treatment of UTI when not warranted. The second QI strategy consists of facility-level, monthly feedback about urine culture usage and reminders of guidelines, which will be given to LTCH staff to address the barrier of perceived risk of negative outcomes when choosing non-testing/treatment. Both QI strategies do not require explicit changes to work processes of LTCH staff, an important and advantageous consideration at a time when the Canadian healthcare sector faces human resource challenges.

The effectiveness of the QI strategies will be evaluated by assessing expected reductions in urine culture orders and antibiotic prescriptions for UTI. Whenever possible, we will also examine the proportion of urine cultures aligned with guidelines before and after intervention. A mixed-methods approach will evaluate the success of the study, with qualitative data helping contextualize quantitative findings.

The purpose of this study is to test novel behavioural AMS interventions in support of optimizing testing and treatment of UTI in LTCHs. The primary quantitative research questions are as follows: 1) What is the baseline usage of urine cultures in participating LTCHs?; and 2) Does implementation of the proposed QI strategies reduce the rates of a) urine cultures, b) antibiotic prescriptions for UTI and c) overall antibiotic prescriptions? Exploratory research questions will examine the baseline proportion of urine cultures aligned with guidelines and what risk factors are associated with collection of urine cultures when not aligned with guidelines. Qualitative data will also be collected to nuance quantitative findings.

## Methods

### Study overview

The study will be conducted in two stages. In the Pilot Stage, the protocol was implemented in a single LTCH for process evaluation (see **Appendix A: Protocol refinements**). The Trial Stage involves implementation in eight other LTCHs across Canada, with the main objective being an outcomes evaluation. The Trial Stage is designed as a stepped-wedge cluster randomized quality improvement study (**Table 1**) using a mixed-method approach. Quantitative data will evaluate the effectiveness of the protocol at reducing both testing and treatment for UTI, and qualitative data will contextualize the findings. Long-term care homes will be randomized to different starting times for the crossover from the control to intervention phases, with staff and residents blinded to their allocation sequence. Here, we present the final protocol, including changes informed by Pilot Stage findings. For a complete list of refinements made to the protocol following the Pilot Stage, refer to Appendix A: Protocol refinements.

**Table 1 t1:** Overview of the stepped-wedge design

LTCH	Cluster	Month 1	Month 2	Month 3	Month 4	Month 5	Month 6	Month 7	Month 8
a	1	C	C	T	I	I	I	I	I
b	1	C	C	T	I	I	I	I	I
c	2	C	C	C	T	I	I	I	I
d	2	C	C	C	T	I	I	I	I
e	2	C	C	C	T	I	I	I	I
f	3	C	C	C	C	T	I	I	I
g	4	C	C	C	C	C	T	I	I
h	4	C	C	C	C	C	T	I	I

Abbreviations: C, Control Phase (usual care is given); I, Intervention Phase (implementation of intervention); LTCH, long-term care home; T, Transition Phase (initiation of intervention)

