### Sample characteristics

A purposive sampling strategy was used to recruit large (approximately 200 residents) LTCHs across Canada. To be eligible, LTCHs had to provide long-term (permanent placement) residential care with 24-hour monitoring and medical assistance. Sample size calculations using Hemming and Taljaard’s approach ((30)) indicated that eight LTCHs across four clusters, observed for a total of eight months, would be sufficient to detect a clinically meaningful 20% reduction in rate of urine culture ordering (6.5 to 5.2 urine cultures per 1,000 resident days) at greater than 80% power and 5% significance level. The effect size is in line with previous studies that observed greater than 25% reduction in urine culture ordering ((31,32)) and is more conservative than 25% reduction used in sample size calculations for a similarly designed trial ((33)).

Two limitations of this trial are its smaller sample size and the purposive sampling technique, which will not provide a representative sample of LTCHs across Canada. However, this is the first pilot study of a novel intervention, so the smaller more homogenous sample will provide initial evidence on the effectiveness of the strategies, which will allow for improvement of the processes and materials.

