### Control Phase

The Control Phase will last between two and five months, depending on cluster number (Table 1). During the Control Phase, usual care will be given to the LTCH residents, and minimum and additional data elements (such as the number of urine cultures ordered and catheter use) will be collected on a monthly basis, as necessary, to answer both the primary and exploratory research questions. The complete list of variables is provided in **Appendix B: Outcome metrics**.

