### Data analysis

A series of descriptive (continuous variables) and frequency analyses (categorical variables) will be conducted to get a global sense of the sample responses.

Analysis will be done at the level of the LTCH as an intention-to-treat analysis. To evaluate research question 1, rate of urine culture (per 1,000 resident days) will be calculated for the retrospective data period. To evaluate research question 2a, a generalized linear mixed-effects model will be used to assess whether or not the intervention has an effect on the rate of urine culture (per 1,000 resident days). The model will include categorical, fixed effects for phase (control/intervention) and for each month to account for secular trends, as well as a random effects for LTCH. Data from the Transition Phase will be excluded from these analyses as we do not consider these data to be clearly Control or Intervention Phase data. To evaluate research questions 2b and 2c, a similar model will be used with the outcome measures rate of antibiotic prescriptions for UTI and total antibiotic prescriptions per 1,000 resident days. Exploratory analyses will use a similar model to evaluate the potential effect of the intervention on rate of urine cultures not aligned with guidelines. Alignment with guidelines will be estimated by comparing the signs and symptoms prompting each urine culture to meet the modified Loeb minimum criteria for UTI for a catheterized or non-catheterized resident ((37,38)).

Thematic analysis will be guided by ethnographic methods and Normalization Process Theory. Taking an iterative approach that draws on Grounded Theory ((35)), open-ended codes will be applied alongside selected evaluative codes developed from a Normalization Process Theory perspective ((57,58)). Ethnographic data reduction techniques will be applied to surface focused insights to support the overarching research questions for the study ((34,36,59)).

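### Table 1's 2/3/1/2 split of homes over the start dates is valid but inefficient for the planned model; 3/1/1/3 would cut the variance of the intervention effect by about 19%

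*Protocol article*

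**What the plan says.** Study overview: "Long-term care homes will be randomized to different starting times for the crossover from the control to intervention phases". Table 1, headed "Overview of the stepped-wedge design", lists homes a and b in group 1, c, d and e in group 2, f alone in group 3, and g and h in group 4. The Transition month is Month 3, 4, 5 or 6 respectively. The article calls these start groups clusters.

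Sample characteristics: the sample is "eight LTCHs across four clusters, observed for a total of eight months", in "large (approximately 200 residents) LTCHs across Canada". The target is a 20% reduction, "6.5 to 5.2 urine cultures per 1,000 resident days", "at greater than 80% power and 5% significance level". No between-home variance or intracluster correlation is given, and the sidedness of the test is not stated.

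Control Phase: "The Control Phase will last between two and five months, depending on cluster number", which agrees with Table 1.

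Data analysis: the model has categorical fixed effects for phase and month and a random effect for home. "Data from the Transition Phase will be excluded from these analyses".

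**The concern.** With categorical month effects, the phase effect draws heavily on months in which some homes are in Control while others are in Intervention. Once Transition months are dropped, Table 1 has only two such months, 4 and 5. Homes in groups 1 and 4 contribute to both. A home in group 2 is in Transition in Month 4, and a home in group 3 is in Transition in Month 5, so each contributes to only one. Table 1 puts four of the eight homes in these two less informative groups and leaves Month 5 resting on two Control homes.

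The number of homes per start date can be chosen without adding homes, months or data, unless site logistics fix it. The article names its small sample as a limitation. The same form of model serves all three rates in research question 2, so the split bears on the precision of each.

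**Working it through.** **Inputs from the article.** Eight homes; Transition in Months 3 to 6; about 200 residents per home; 6.5 falling to 5.2 cultures per 1,000 resident days; 5% significance; month and phase fixed effects; home random effect; Transition excluded.

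**Assumptions.** Equal home sizes; 30.4 days per month, so 200 × 30.4 = 6,080 resident days per home-month; Poisson counts; two-sided test. The between-home SD on the log scale is not given, so it is varied.

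**Step 1: concurrent homes.**

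| | Table 1 (2/3/1/2) | 3/1/1/3 |
|---|---|---|
| Month 4, Intervention v Control | 2 v 1+2 = 3 | 3 v 1+3 = 4 |
| Month 5, Intervention v Control | 2+3 = 5 v 2 | 3+1 = 4 v 3 |
| Control home-months | 4+9+4+10 = 27 | 6+3+4+15 = 28 |
| Intervention home-months | 10+12+3+4 = 29 | 15+4+3+6 = 28 |

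Month 3 has no Intervention home. In Month 6 the last group is in Transition, so no Control home remains.

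**Step 2: variance.** Expected counts per home-month are 6.08 × 6.5 = 39.5 in Control and 6.08 × 5.2 = 31.6 in Intervention. The log-rate variances are therefore 1/39.5 and 1/31.6. For each home, V = diag(these variances) + SD² in every cell. The variance of the phase effect is the phase element of (Σ Z′V⁻¹Z)⁻¹, where Z holds phase and month indicators and Transition rows are removed.

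**Step 3: power** = Φ(ln(1.25)/SE − 1.96), with ln(1.25) = 0.2231.

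| Between-home SD | SE, Table 1 | SE, 2/2/2/2 | SE, 3/1/1/3 | Power, Table 1 | Power, 3/1/1/3 | Variance ratio, 3/1/1/3 to Table 1 |
|---|---|---|---|---|---|---|
| 0 | 0.1032 | 0.1032 | 0.0911 | 58% | 69% | 0.780 |
| 0.1 | 0.1139 | 0.1136 | 0.1018 | 50% | 59% | 0.799 |
| 0.3 | 0.1186 | 0.1182 | 0.1069 | 47% | 55% | 0.813 |
| 1.0 | 0.1194 | 0.1190 | 0.1078 | 46% | 54% | 0.815 |

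At SD 0.3 for Table 1: 0.2231/0.1186 − 1.96 = −0.08, and Φ(−0.08) = 0.47. For 3/1/1/3: 0.2231/0.1069 − 1.96 = 0.13, and Φ(0.13) = 0.55. The variance cut is 1 − 0.813 = 0.187, or about 19%.

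**The plan's own figure.** Power above 80% is not reproduced under this model: Table 1 gives 58% at best, or 70% one-sided with no between-home variation. A figure above 80% appears if month effects are dropped (above 99%), or if Transition counts as Intervention (84% two-sided with no between-home variation; about 82% one-sided at a between-home coefficient of variation of 0.2 to 0.4). The article does not show which calculation was used.

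**Step 4: other splits.** Of the 35 splits with at least one home per start date, 3/1/1/3 has the smallest variance. At SD 0.3, 2/2/2/2 has ratio 0.994 to Table 1, so the gain comes from loading the first and last dates, not from equalising the groups.

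**Step 5: sensitivity of the variance cut.**
- Home-by-month SD up to 0.15, between-home SD 0.1 to 1.0: 18% to 21%.
- Overdispersion 1.5 to 3: about 19%.
- Transition kept as its own level, SD 0.3: about 16%.
- Autoregressive home correlation of 0.7 to 0.95 per month: 14% to 17% at SD 0.3, down to about 9% at SD 1.0.
- Transition counted as Intervention, SD 0.3: about 8%.
- No month effects: no gain; 3/1/1/3 is up to 5% worse.

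**The case against.** Table 1 contains no error. It agrees with the stated homes, groups, months and Control durations, and it is as precise as the usual balanced split. The article is condensed, so reasons such as site readiness or launch capacity may sit in the full protocol. The abstract says the protocol is already being implemented, so re-allocation may be too late. The change is not free either: each launch needs coordination and staff education from the research team, and 3/1/1/3 has two three-home launch months (3 and 6) where Table 1 has one (4). It also has two single-home start groups instead of one. The gain depends on the analysis, and power stays well below the stated level.

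All of this stands, and it makes the point an improvement in efficiency, not a correction. It does not remove the point. Table 1 is a choice the article fixes, the 19% applies to the model the article specifies, and Study overview describes randomisation as still to come. The single-home groups are not a practical weakness for precision: at SD 0.3, losing any one home leaves 3/1/1/3 with 47% to 52% power, against 36% to 45% for Table 1.

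A reader might infer that the uneven split is a mistake, or that it explains the power shortfall. The documents support neither. Equal groups would be no better, and the best split still gives only about 55%.

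**Conclusion.** The point holds as a low-cost improvement. Under the stated analysis, 3/1/1/3 cuts the variance of the intervention effect by about 19% (18.5% to 22% over all between-home SDs tried). That is a 10% smaller standard error and about 8 percentage points of power at SD 0.3. The figure rests on equal homes of 200 residents, Poisson counts, a two-sided 5% test, fitted month effects and exclusion of Transition months. It shrinks to about 15% or 8% under the alternatives above and is absent without month effects. It should not be read as a defect in the validity of the trial, as cost-free, or as a route back to power above 80%.

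**What to change.** If start dates are not yet assigned and site logistics allow, randomise the eight homes 3/1/1/3 to the existing start months (Transition in Months 3, 4, 5 and 6), and compute the stated power from that table. This needs no extra homes, months or data. The cost is a second three-home launch month and a second single-home start group.

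If allocation is already fixed, keep Table 1 and restate the power or precision in Sample characteristics from the actual 2/3/1/2 table with Transition excluded. Give the assumed between-home variance and the sidedness of the test. On the assumptions here that is about 47% two-sided at a between-home SD of 0.3, and about 58% with no between-home variation. This costs only a recalculation and a revised sentence.

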### Sample characteristics

A purposive sampling strategy was used to recruit large (approximately 200 residents) LTCHs across Canada. To be eligible, LTCHs had to provide long-term (permanent placement) residential care with 24-hour monitoring and medical assistance. Sample size calculations using Hemming and Taljaard’s approach ((30)) indicated that eight LTCHs across four clusters, observed for a total of eight months, would be sufficient to detect a clinically meaningful 20% reduction in rate of urine culture ordering (6.5 to 5.2 urine cultures per 1,000 resident days) at greater than 80% power and 5% significance level. The effect size is in line with previous studies that observed greater than 25% reduction in urine culture ordering ((31,32)) and is more conservative than 25% reduction used in sample size calculations for a similarly designed trial ((33)).

Two limitations of this trial are its smaller sample size and the purposive sampling technique, which will not provide a representative sample of LTCHs across Canada. However, this is the first pilot study of a novel intervention, so the smaller more homogenous sample will provide initial evidence on the effectiveness of the strategies, which will allow for improvement of the processes and materials.

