4	Narrowing of prospective data collection	The protocol now includes collection of signs and symptoms prompting all urine culture orders during the Control, Transition and Intervention Phases. This allows an estimation of the proportion of cultures that are aligned with guidelines. A measure of alignment with guidelines will allow for a more precise measure of AMS compared to rate of urine culture alone. Alignment with guidelines will be used as an exploratory evaluation of the success of the trial (pre-post comparison) as well as a component of the feedback report. To balance the additional workload to LTCHs collecting this data, the protocol also limits the previously required monthly facility-level demographic data from all residents of the LTCH to only those who received a urine culture. The previous monthly facility-level demographics provided little additional value to the cross-sectional demographic data collected with the retrospective data. If some LTCHs are unable to provide signs and symptoms data, we will 1) report this finding, which will highlight an important knowledge gap, 2) remain adequately powered to evaluate the study using rate of urine culture order and 3) antibiotic prescription for UTI as previously planned.
5	Updates to feedback letter content	The protocol now calls for the feedback letter to provide a self-comparison of LTCH urine culture order rate over time, as well as an estimate of the proportion of urine culture orders that were aligned with guidelines. Previously, the protocol called for a peer-comparison of urine culture order rate between the LTCHs included in the Trial Stage, as well as comparison with historical data. The change avoids limitations of inter-home comparisons and allows for a focus on self-comparison in the spirit of continual improvement.

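### The stated power of more than 80% for a 20% reduction is not delivered by Table 1 under the stated model: about 47%, and at most about 58% with Poisson counts

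*Protocol article*

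**What the plan says.** In the Protocol article, Sample characteristics, the homes are "large (approximately 200 residents) LTCHs across Canada". A design of "eight LTCHs across four clusters, observed for a total of eight months" is said to be enough to detect a 20% fall in "urine culture ordering (6.5 to 5.2 urine cultures per 1,000 resident days) at greater than 80% power and 5% significance level". A published stepped-wedge method is cited. The article gives no intracluster correlation, no between-home or month-to-month variance, and no account of how Transition months entered the calculation.

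The Data analysis section then fixes the analysis: "The model will include categorical, fixed effects for phase (control/intervention) and for each month to account for secular trends", plus a random effect for home, and "Data from the Transition Phase will be excluded from these analyses".

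Appendix A, change 4, relies on the power claim. If some homes cannot supply signs and symptoms data, the trial will still "remain adequately powered to evaluate the study using rate of urine culture order".

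**The concern.** The home size, rates, layout, model and Transition exclusion all stand in the article, so the power claim can be tested against them. With Transition removed, Months 1–3 have no Intervention home and Months 6–8 have no Control home. Because the model fits a separate effect for every month, most of the contrast between phases is confounded with calendar time and is lost.

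If the real power is well under 80%, a non-significant result could be taken as evidence that the strategies do not work, when the trial was never likely enough to show a 20% reduction. The fallback in Appendix A rests on the same claim.

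**Working it through.** **Inputs from the article.** About 200 residents per home; 6.5 and 5.2 cultures per 1,000 resident days (rate ratio 0.80); 5% level; Table 1 with 2, 3, 1 and 2 homes in its four clusters; categorical months; random home effect; Transition excluded.

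**Assumptions, because the article does not give them.** 30.4 days per month; two-sided test; Poisson counts; between-home SD on the log scale from 0 to 1.0; extra home-by-month SD from 0 upwards.

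**Cells.** Removing one Transition month from each of the 8 homes leaves 64 − 8 = 56 home-months, 27 Control and 29 Intervention. Both phases appear only in Month 4 (3 Control, 2 Intervention) and Month 5 (2 Control, 5 Intervention).

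**Expected counts per home-month.** 200 × 30.4 = 6,080 resident days. Control: 6.5 × 6.08 = 39.5. Intervention: 5.2 × 6.08 = 31.6.

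**Target.** |ln 0.80| = 0.2231. A power of 80% needs SE = 0.2231 / (1.96 + 0.84) = 0.0797.

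**No between-home variation (can be checked by hand).** Only the two mixed months are then informative.
- Month 4 variance: 1/(3 × 39.52) + 1/(2 × 31.62) = 0.00843 + 0.01581 = 0.02425; precision 41.2.
- Month 5 variance: 1/(2 × 39.52) + 1/(5 × 31.62) = 0.01265 + 0.00633 = 0.01898; precision 52.7.
- SE = 1/√(41.2 + 52.7) = 0.1032. Power = Φ(0.2231/0.1032 − 1.96) = Φ(0.20) = 58%.

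**With between-home variation.** The variance of the phase effect is the corresponding diagonal element of (X′V⁻¹X)⁻¹. X holds phase and eight month indicators. V has 1/(expected count) on the diagonal plus the between-home variance shared by cells of one home. Power is Φ(0.2231/SE − 1.96).

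| Between-home SD | Power, Poisson | Power, binomial variance |
|---|---|---|
| 0 | 58% | 67% |
| 0.1 | 50% | 58% |
| 0.2 | 48% | 55% |
| 0.3 (Poisson SE 0.119) | 47% | 55% |
| 1.0 | 46% | 54% |

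The binomial column replaces 1/μ by (1 − μ/200)/μ, where μ is the expected count. Poisson simulation (1,500 runs) gave 47% at SD 0.3 and 56% at SD 0.

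**Extra home-by-month variation, at between-home SD 0.3.** SD 0.10 gives 37%; SD 0.15 gives 29%.

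**What would give 80%.** At about 200 residents, a reduction of about 26% (between-home SD 0) to 29% (SD 0.3). For a 20% reduction at SD 0.3, about 450 residents per home.

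**Trying to recover the stated figure.** Its variance inputs are not given, so it cannot be reproduced directly. Figures at or above 80% appear when the calculation departs from the stated analysis:
- Transition counted as Intervention, months kept: 84% (Poisson, SD 0) falling to 72% (SD 0.3); with binomial variance, 90% falling to 80%.
- Month effects dropped, Transition excluded: above 99%.

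A one-sided 5% test under the stated model gives only 59–70%.

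**The case against.** The strongest reply is that the article is a condensed account. The variance inputs may sit in a full protocol or analysis plan, and a reviewer should not put assumed values in place of the sponsor's. This stands as far as any single figure is concerned: a between-home SD of 0.3 is an assumption. It does not rescue the claim, because power stays between 46% and 58% over the whole range of between-home SD under Poisson counts, and home-by-month variation only lowers it. Counts would have to vary far less than Poisson to reach 80%. The variance ratio needed is (0.0797/0.1186)² = 0.45 at SD 0.3, or (0.0797/0.1032)² = 0.60 with no home differences.

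The article also lists its smaller sample as a limitation and calls the results initial evidence. That softens the harm but leaves the power claim in place.

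Four stronger readings are tempting, and the documents do not support them:
- That 47% is the best case. The Poisson ceiling is 58%, and binomial variance allows 67%. The article describes a fairly homogeneous sample, so small home differences cannot be ruled out.
- That a true 20% reduction would be missed more often than found. This is so at SD 0.2 or above under Poisson counts, but not with little between-home variation or under binomial variance.
- That Months 4 and 5 explain everything. At SD 0.3 those two months alone give 14.5% power, against 47% with all months. The other months help by estimating each home's level.
- That the sponsor's calculation is shown to have ignored the Transition exclusion or the month effects. The variants above suggest a mismatch but do not prove it.

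**Conclusion.** The power statement is wrong as written. At the stated home size, rates, layout and model, power for a 20% reduction is about 47% with ordinary between-home differences and at most about 58% with none, under Poisson counts and a two-sided 5% test. Binomial variance gives about 54–67%, and modest home-by-month variation at between-home SD 0.3 brings it to about 29–37%. No between-home variance tried reaches 80%. The exact figure depends on variances that the article does not give; the shortfall does not.

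**What to change.** Redo the power calculation for Table 1 under the model in Data analysis: month effects, random home effect, Transition excluded. Report the between-home and home-by-month variance assumed, and the reduction detectable at 80% power. Remove the claims of sufficient power (Sample characteristics) and adequate power (Appendix A, change 4) unless the recalculation supports them. State that a non-significant result is inconclusive. The cost is a recalculation, some wording, and a less favourable power statement.

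Optionally, add a supplementary or sensitivity analysis on data already planned. Keeping Transition months as a third phase level gives about 52% at between-home SD 0.3 (SE 0.111). Adding the retrospective year as one further all-Control period gives about 64% (SE 0.096), or about 51% if home-by-month SD is 0.10. This assumes a common Transition effect across homes and home differences that stay stable over time. It does not restore 80%, so it does not replace the restatement.
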